### Definition of heart failure

Clinical HF will be defined using the European Society of Cardiology guidelines: “HF is a syndrome in which the patients should have the following features: symptoms and signs of HF and objective evidence of an abnormality of the structure or function of the heart at rest” [14].

### Medical note review

Medical note review, obtained from GP notes, on recruited patients will be performed at 6 and 12 months. Data on medications, hospital and nursing home admissions, A&E attendance, referrals presentation with new symptoms/complications and death will be recorded. We shall use these data (i.e. clinical events and resource use) in the economic modelling of outcomes associated with the use of the CDR.

### Sample size

Thirty urban and rural general practices in the West Midlands will be asked to participate to recruit 500 symptomatic patients. A search of routine practice morbidity data suggest that in a practice of 6,000 patients, around 60 patients over age 55 per year will present with new onset breathlessness. Breathlessness is the commonest of the three most likely symptoms of heart failure (others are lethargy or ankle swelling) and therefore these estimates on the rate that symptoms present will be the minimum rates. Assuming a 60% response rate then it would take at least nine months to recruit at least 25 such patients per practice. All practices will stop active patient recruitment at the end of 18 months. Calculations are based on sensitivity of 94% and specificity of 48% obtained from application of the CDR in our HTA funded individual patient data meta-analysis [40] and the prevalence of heart failure in a symptomatic population of 30%. A sample size of 500 patients with HF symptoms will therefore be sufficient to estimate the sensitivity of the CDR to within 4% and specificity to within 6% at the 95% confidence level.

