## Methods/design

### Study design and setting

REFER is a prospective, observational, diagnostic validation study of a CDR, natriuretic peptide or their combination, for diagnosing heart failure in primary care. The study will be conducted in 30 urban and rural primary care practices in Birmingham, West Midlands, England.

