### Recruitment rate

A total of 500 patients will be recruited, 25 per practice. To allow for delays, the target recruitment rate will be three patients per practice per month, with expected recruitment completed within 18 months. We shall monitor recruitment rates and if we fail to achieve the target accrual rate, additional practices will be invited to participate.

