### Clinical judgment

During the initial consultation, GPs will have identified a patient as eligible for referral to one of the two research assessment clinics (i.e. recent new onset shortness of breath, lethargy or ankle oedema of over 48 hours duration). They will then complete the two clinical judgment sections of the online web-based Case Report Form: 1) details of symptoms, history and patient information, including the predictive clinical features of the CDR; 2) whether they would have made a clinical diagnosis of HF or not and what they would have done routinely with this patient (i.e. investigate, initiate referral, treat, follow-up). Following diagnostic assessment at the research assessment clinic, the NP results will be fed back to GPs and based on those results, GPs will be asked what they would do (refer or not refer to Echo) and if they would amend their original diagnosis.

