### Statistical analysis

Data will be analysed using SAS and STATA software. Patients with symptoms of HF that are referred to Echo via the CDR will be classed as Test disease present and the remaining patients classed as Test disease absent. The Observed disease present or absent will be determined by the expert panel following Echo and other clinical assessments. Crosstabulation of Test versus Observed disease status will enable calculation of sensitivity (true positive rate), specificity (true negative rate), positive predictive value (PPV: proportion with a positive test result who actually have the target condition), negative predictive value (NPV: proportion with a negative test result who do not have the target condition), and likelihood ratios for testing the performance of the CDR. 95% confidence intervals for these performance statistics will be calculated using the binomial exact method.

To confirm whether the NT-proBNP cut-offs in the CDR are optimal in the real life clinical setting, an additional ROC curve analysis of NT-proBNP to predict HF will be performed. Analysis will compare the CDR performance against the step 1 reference test alone; against the step 1 reference test plus clinical features of the CDR (step 2); and against the step 1 reference test plus the CDR and the NT-proBNP result (the reference standard, step 3). Step 3 is the primary reference standard for analysis. This will allow us to: 1) quantify the effects of any incorporation bias; 2) explore the impact that availability of NT-proBNP test result would have on the reference standard diagnosis of HF. Comparison of the GPs’ and researcher’s clinical findings (lung crepitations, ankle oedema, decision to refer to Echo) will be assessed by the kappa statistic. Logistic regression will be used to identify which diastolic parameters of echocardiography are independently associated with the diagnosis of heart failure with preserved ejection fraction.

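### The stated 4-point precision for sensitivity is a normal-approximation figure; the planned exact interval has its lower limit 5.1 points below the estimate, and specificity meets its 6 points only if clustering by practice is slight.

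*Protocol article*

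**What the plan says.** The Sample size section gives its inputs: "Calculations are based on sensitivity of 94% and specificity of 48"%, and "the prevalence of heart failure in a symptomatic population of 30"%. From these it concludes: "A sample size of 500 patients with HF symptoms will therefore be sufficient to estimate the sensitivity of the CDR to within 4"%, with 6% for specificity, both at 95% confidence. It names no formula.

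The Statistical analysis section does fix a method for what will be reported: "95% confidence intervals for these performance statistics will be calculated using the binomial exact method".

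On where patients come from, Study design and setting says: "The study will be conducted in 30 urban and rural primary care practices". Recruitment rate says: "A total of 500 patients will be recruited, 25 per practice", and 500/25 is 20 practices. Both counts are carried through below. Neither the sample size text nor the analysis text mentions an ICC, a design effect or an interval that allows for practice.

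**The concern.** Sensitivity is a primary outcome, and the rule decides who is sent for echocardiography and who is not. Its main risk is missed heart failure, so readers will look first at the lower confidence limit for sensitivity. A promise of 4 points around 94% suggests a lower limit near 90%. With sensitivity near 94% an exact interval is asymmetric, and its longer arm is the lower one. The stated precision may therefore fail on the side that matters.

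The second issue is independence. Both the planning figure and the plain exact interval treat the 500 patients as unrelated. GPs judge eligibility and record "details of symptoms, history and patient information, including the predictive clinical features of the CDR". The Background itself notes that doctors differ in eliciting symptoms and signs. Some correlation within practices is plausible, and if it is present a plain binomial interval understates the uncertainty.

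**Working it through.** **Inputs.** From the Sample size section: N = 500, prevalence 30%, sensitivity 94%, specificity 48%. These give 0.30 × 500 = 150 patients with heart failure and 350 without. Expected counts are 0.94 × 150 = 141 true positives and 0.48 × 350 = 168 true negatives.

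**1. The plan's own figures.** The normal-approximation half-width is 1.96 × √(p(1−p)/n).
- Sensitivity: 1.96 × √(0.94 × 0.06/150) = 3.8 points, within the stated 4.
- Specificity: 1.96 × √(0.48 × 0.52/350) = 5.2 points, within the stated 6.

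Both stated figures reproduce.

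**2. The planned method.** Exact (Clopper-Pearson) two-sided 95% intervals:
- Sensitivity 141/150: 88.9% to 97.2%, or −5.1/+3.2 points, mean half-width 4.15.
- Specificity 168/350: 42.7% to 53.4%, or −5.3/+5.4 points.

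The long lower arm is not peculiar to the expected count. With 150 heart failure patients, an observed sensitivity in this range has an exact lower arm of 4 points or less only if at least 147 test positive. At a true sensitivity of 94% that has a probability of about 2%.

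**3. Clustering, with an assumed ICC.** The article gives none, so a range is shown. Design effect = 1 + (m − 1) × ICC, where m is the number of relevant patients per practice. With 30 practices m is 150/30 = 5 (heart failure) and 350/30 = 11.7 (no heart failure). With 20 practices it is 7.5 and 17.5. Exact limits are recomputed at n divided by the design effect.

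| ICC | Practices | Design effect, sens. / spec. | Sensitivity, lower arm | Specificity, half-width |
|---|---|---|---|---|
| 0.01 | 30 | 1.04 / 1.11 | 5.2 | 5.6 |
| 0.02 | 30 | 1.08 / 1.21 | 5.3 | 5.9 |
| 0.05 | 30 | 1.20 / 1.53 | 5.7 | 6.7 |
| 0.01 | 20 | 1.07 / 1.17 | 5.3 | 5.8 |
| 0.02 | 20 | 1.13 / 1.33 | 5.5 | 6.2 |
| 0.05 | 20 | 1.33 / 1.83 | 6.1 | 7.3 |

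**4. Where specificity passes 6 points.** The exact half-width without clustering is 5.36, so the tolerable design effect is about (6/5.36)² = 1.25. The break-even ICC is about 0.25/10.67 = 0.023 to 0.024 with 30 practices (the range reflects rounding and whether the limits are scaled or re-solved) and 0.25/16.5 = 0.015 with 20.

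**5. Coverage of the plain exact interval.** Beta-binomial simulation, 30 practices:
- Sensitivity: 96.3% under independence; with clustering 95.9% at ICC 0.01, 95.6% at 0.02, 95.1% at 0.03 and 94.3% at 0.05.
- Specificity: about 93% at ICC 0.02 and 89% at 0.05.

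With 20 practices coverage is somewhat lower: sensitivity 95.1% at ICC 0.02 and 94.3% at 0.03; specificity about 91% at 0.02 and 86% at 0.05.

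**The case against.** The strongest reply is that nothing has been miscalculated. Both planning figures follow from the plan's own inputs, the Sample size section does not say that it used the exact method, and planning with a symmetric half-width while reporting exact intervals is ordinary practice. The mean exact half-width of 4.15 also rounds to 4. No test, threshold or stopping decision hangs on the 4 points, and the reported interval will itself show the longer lower arm. All of this stands. It makes the point a mismatch of methods with a one-sided shortfall of about 1 point. It does not remove the mismatch between a stated precision and the interval that will be reported for a primary outcome.

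On clustering, the reply is that correlation within practices is possible but not established. Inclusion is meant to be consecutive whether or not heart failure is suspected. Research staff at two clinics also examine every patient. NT-proBNP, sex and history of infarction do not depend on a GP's examination. One panel sets the reference diagnosis. This also stands, so the clustering part must be conditional. Because the exact interval is conservative for sensitivity, low ICCs do little harm there, and the exposure lies mainly in specificity.

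It can also be said that cluster-adjusted intervals are often left to the statistical analysis plan, which is not shown. The article, however, does name the interval method, and it names one that assumes independence. That statement can fairly be reviewed.

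**Conclusion.** The point holds as a method mismatch of modest size. Under the exact method that the article fixes, and assuming independent patients, 94% sensitivity in 150 heart failure patients gives a lower limit 5.1 points below the estimate, not 4. Specificity meets its 6 points with a little to spare (about 5.4).

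The clustering part rests on an ICC that the article does not give. Above about 0.024 (30 practices) or 0.015 (20 practices) the 6 points for specificity would be exceeded, and the plain exact interval would undercover. Sensitivity coverage stays near nominal up to an ICC of about 0.03 with 30 practices, or about 0.02 with 20.

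Three stronger readings are tempting and not supported:
- That the 4% is an arithmetic error. It reproduces at 3.8 points from the stated inputs.
- That both stated margins are too narrow. The 6 points for specificity is wider than the exact 5.4 unless clustering is present, and its presence is not shown.
- That the study is too small. A 4-point exact lower arm would need about 221 heart failure patients (221/0.30 = about 737 in total), but the article does not say that its 4 points refers to the lower arm.

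**What to change.** In the Sample size section, replace the 4% and 6% by the expected exact 95% intervals, 88.9% to 97.2% for sensitivity and 42.7% to 53.4% for specificity. Label them as assuming 150 and 350 independent patients. Add one line for an assumed ICC of 0.01 to 0.05: with 30 practices, a sensitivity lower arm of 5.2 to 5.7 points and a specificity half-width of 5.6 to 6.7; with 20 practices, 5.3 to 6.1 and 5.8 to 7.3.

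In the Statistical analysis section, keep the exact interval and add one that allows for practice, chiefly for specificity. Clopper-Pearson limits on the effective sample size, or a bootstrap that resamples practices, would serve.

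The cost is a slightly less favourable statement of precision, possibly slightly wider reported intervals, and a few lines of code. No extra patients are needed.

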### Statistical analysis

Data will be analysed using SAS and STATA software. Patients with symptoms of HF that are referred to Echo via the CDR will be classed as Test disease present and the remaining patients classed as Test disease absent. The Observed disease present or absent will be determined by the expert panel following Echo and other clinical assessments. Crosstabulation of Test versus Observed disease status will enable calculation of sensitivity (true positive rate), specificity (true negative rate), positive predictive value (PPV: proportion with a positive test result who actually have the target condition), negative predictive value (NPV: proportion with a negative test result who do not have the target condition), and likelihood ratios for testing the performance of the CDR. 95% confidence intervals for these performance statistics will be calculated using the binomial exact method.

To confirm whether the NT-proBNP cut-offs in the CDR are optimal in the real life clinical setting, an additional ROC curve analysis of NT-proBNP to predict HF will be performed. Analysis will compare the CDR performance against the step 1 reference test alone; against the step 1 reference test plus clinical features of the CDR (step 2); and against the step 1 reference test plus the CDR and the NT-proBNP result (the reference standard, step 3). Step 3 is the primary reference standard for analysis. This will allow us to: 1) quantify the effects of any incorporation bias; 2) explore the impact that availability of NT-proBNP test result would have on the reference standard diagnosis of HF. Comparison of the GPs’ and researcher’s clinical findings (lung crepitations, ankle oedema, decision to refer to Echo) will be assessed by the kappa statistic. Logistic regression will be used to identify which diastolic parameters of echocardiography are independently associated with the diagnosis of heart failure with preserved ejection fraction.

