### Primary and secondary endpoints

Primary outcomes include:

• Test performance of the CDR, estimating the sensitivity and specificity, positive predictive value and negative predictive value of the CDR for diagnosis of HF in symptomatic patients presenting with shortness of breath, lethargy, or ankle oedema of over 48 hours duration

• Test performance of the diagnostic accuracy of NT-proBNP for diagnosis of HF in symptomatic patients, including sensitivity, specificity, positive predictive value and negative predictive value

• Proportion of patients with LVSD or not (ejection fraction <40%) and HF or not

Secondary outcomes include:

• Combination of the CDR and NT-proBNP

• Modelling of CDR test performance and epidemiological data to ascertain the most cost effective strategy in the diagnosis of HF in primary care, incorporating data on quality of life (EQ-5D and SF12 questionnaires), clinical events and health care resource use

• Reliability of GP clinical judgment alone in diagnosing HF

• Reliability of individual clinical features

• Reliability of ECG interpretation

• Estimation of the best performing cut-offs for NT-proBNP to maximise diagnostic yield and for maximizing cost-effective referrals

• Determine the use of variable echocardiographic markers of diastolic function in the diagnosis of HF with preserved ejection fraction

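### The binomial exact method is assigned to every listed accuracy statistic, but it is not defined for the likelihood ratios; a minor error confined to supplementary intervals

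*Protocol article*

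**What the plan says.** In the protocol article's Statistical analysis section, CDR referral status is cross-tabulated against the expert panel's diagnosis. The section names the measures to be taken from that table: sensitivity, specificity, PPV, NPV, "and likelihood ratios for testing the performance of the CDR". The next sentence fixes the interval method for all of them: "95% confidence intervals for these performance statistics will be calculated using the binomial exact method". The likelihood ratios are the last item before that sentence, so on a plain reading it covers them. The article makes no exception for them and names no other interval method.

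Two other sections bear on the size of the point:

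- Primary and secondary endpoints defines the primary CDR outcome as "estimating the sensitivity and specificity, positive predictive value and negative predictive value of the CDR". Likelihood ratios are in neither the primary nor the secondary list.
- Sample size takes "sensitivity of 94% and specificity of 48% obtained from application of the CDR in our HTA funded individual patient data meta-analysis", a heart failure prevalence of 30% and 500 patients, and concludes that this is enough to "estimate the sensitivity of the CDR to within 4% and specificity to within 6% at the 95% confidence level".

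**The concern.** A binomial exact interval needs a count x out of a fixed n. Sensitivity, specificity, PPV and NPV each have that form. The likelihood ratios do not:

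- LR+ = sensitivity / (1 − specificity)
- LR- = (1 − sensitivity) / specificity

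Each divides a proportion from the heart failure group by a proportion from the group without heart failure. LR+ normally exceeds 1, so it cannot be a binomial proportion at all. The article is not silent on the method, which would be a detail left to an analysis plan. It names a method that does not fit one of the listed statistics.

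An analyst who follows the text must therefore improvise. The resulting interval for a nominally prespecified statistic depends on how that is done, and its coverage need not be 95%. The CDR is to be compared with the panel diagnosis at each of three reference-standard steps, so the same problem could recur at each step.

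**Working it through.** **Inputs** (all from Sample size): N = 500; prevalence 30%, so 150 with heart failure and 350 without; sensitivity 0.94; specificity 0.48. Expected table: TP = 141, FN = 9, TN = 168, FP = 182.

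**Step 1. Reproduce the plan's own precision.** Normal-approximation half-widths, 1.96 × √(p(1−p)/n):

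- Sensitivity: 1.96 × √(0.94 × 0.06 / 150) = 3.8 points (stated: within 4%)
- Specificity: 1.96 × √(0.48 × 0.52 / 350) = 5.2 points (stated: within 6%)

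The inputs reproduce the stated figures.

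**Step 2. Exact limits where the method applies** (Clopper-Pearson):

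- Sensitivity 141/150: 0.8892 to 0.9722
- Specificity 168/350: 0.4266 to 0.5337

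**Step 3. Point estimates of the likelihood ratios.**

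- LR+ = 0.94 / 0.52 = 1.81
- LR- = 0.06 / 0.48 = 0.125

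There is no single x/n to enter for either, so the stated method returns nothing directly.

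**Step 4. A method that fits: log (delta) intervals.**

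- SE(log LR+) = √(1/141 − 1/150 + 1/182 − 1/350) = 0.055. The 95% CI is 1.81 × exp(±1.96 × 0.055) = 1.62 to 2.01.
- SE(log LR-) = √(1/9 − 1/150 + 1/168 − 1/350) = 0.328. The 95% CI is 0.125 × exp(±1.96 × 0.328) = 0.066 to 0.238.

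**Step 5. Nearest literal adaptation: put both sets of exact limits into the ratio.**

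- LR+: 0.8892 / (1 − 0.4266) = 1.55, to 0.9722 / (1 − 0.5337) = 2.09
- LR-: (1 − 0.9722) / 0.5337 = 0.052, to (1 − 0.8892) / 0.4266 = 0.260

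**Step 6. Coverage.** This was found by enumerating every outcome of two independent binomials (n = 150 and n = 350) at the planning values. An empty FN cell was replaced by 0.5 in the log method for LR-.

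| Statistic | Method | 95% interval | Width | Coverage |
|---|---|---|---|---|
| LR+ | log | 1.62 to 2.01 | 0.393 | 95.0% |
| LR+ | combined exact limits | 1.55 to 2.09 | 0.534 (36% wider) | 99.2% |
| LR- | log | 0.066 to 0.238 | 0.172 | 95.7% |
| LR- | combined exact limits | 0.052 to 0.260 | 0.208 (21% wider) | 98.6% |

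**The case against.** The strongest reply is that nothing declared in the protocol depends on these intervals, and that reply stands. The primary measures are the four proportions, for which the exact method is right. The sample size rests on sensitivity and specificity. The decision tree in Health economic analysis needs the probability of referral in patients with and without heart failure, that is, sensitivity and 1 − specificity. Sensitivity and NPV already address the rule-out question, with correctly specified intervals. For LR-, 0.052 to 0.260 and 0.066 to 0.238 both lie well below 1 and support the same conclusion.

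It can also be said that one sentence of a condensed article swept in one item too many, and that a competent analyst would use a ratio method anyway. That is plausible, but it would mean departing from the written method. It limits the severity without making the sentence correct.

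A reader might infer something stronger: that the plan would produce badly misleading likelihood-ratio intervals. Taking exact limits for sensitivity and treating specificity as known does give an LR+ interval with only about 56% coverage. But the article nowhere suggests that device, so this figure is not a consequence of its text. The same device covers about 96.4% for LR-, close to the log method's 95.7%. Another improvisation, an exact binomial on the numerator count given all test positives (for LR-, all test negatives), is conservative: LR+ 1.44 to 2.26 (coverage above 99.9%) and LR- 0.056 to 0.243 (97.4%). Serious undercoverage therefore arises only for LR+, and only under a workaround that the plan does not propose.

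**Conclusion.** The point holds as a minor error of specification. As worded, the binomial exact method is assigned to LR+ and LR-, for which it is not defined, and no alternative is given. That conclusion follows from the form of the statistics and does not depend on any planning value.

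The size does depend on them. With 150 and 350 patients, sensitivity 94% and specificity 48%, the nearest literal adaptation gives intervals 36% (LR+) and 21% (LR-) wider than the log method, with coverage of about 99% and 98.6% instead of 95%. At these values the error is towards caution. Other values of sensitivity, specificity or prevalence would change the figures.

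Only the supplementary likelihood-ratio intervals are affected. The likelihood-ratio point estimates, the primary outcomes, the sample size and the economic model are not. The analysis plan, if one exists, was not at hand; if it already names a ratio method, only the protocol wording needs to be aligned.

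**What to change.** In Statistical analysis, restrict the binomial exact method to sensitivity, specificity, PPV and NPV. Add that 95% confidence intervals for LR+ and LR- will use a method for the ratio of two independent proportions: the log (delta) method, with

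- SE(log LR+) = √(1/TP − 1/n_HF + 1/FP − 1/n_nonHF)
- SE(log LR-) = √(1/FN − 1/n_HF + 1/TN − 1/n_nonHF)

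or a score interval for the ratio if a cell is small. The cell to watch is FN, expected to be 9 at the planning values. Apply the same rule at each of the three reference-standard steps.

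The cost is one sentence. The calculation uses the same 2×2 table and needs no new data and no change to the sample size.
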